### 10.8 Missed Dosing Instruction

In the event of a missed dose the outstanding tablet(s) should be taken as soon as it becomes known to the participant a dose had been missed (morning, afternoon or evening dose). If a morning, afternoon or evening dose is missed, the participant to proceed to the subsequent dose that day e.g. a participant misses the morning dose they should proceed to the afternoon dose and evening dose that day and should continue their dosing regimen the subsequent day.

Participants should try and ensure every attempt should be made to ensure consistency in the time of study drug administration during the course of the study.

### 10.9 Overdose of Trial Medication

Should a participant take an overdose that exceeds the recommended dose described in the protocol and experiences any adverse event(s) that may relate to an overdose the participant must inform the PI or PI-delegated member of the research team immediately who will then follow up on their medical care as needed. It will be the opinion of the PI to decide whether the participant should be withdrawn from the study or whether the IMP should be reintroduced.

Each overdose will be recorded and the Sponsor will be notified of the overdose on the deviation log. Overdoses will be observed by the research team being instructed by the participant and pill counts on specific study visits, Visit 5 (day 93), Visit 6 (day 186) and the early termination visit, if applicable.

### **10.10 Dispensing**

The NHNN Pharmacy will dispense the IMP in accordance to the SoDA. Each participant will be dispensed 3 months' supply of IMP at visit 3 (day 1) and visit 5 (day 93) to last at least until the next study visit, along with instructions to use.

### **10.11 IMP Discontinuations**

Based on the known good safety profile of ambroxol no clinical significant adverse reactions are expected in this study. However individual participants may be discontinued from treatment at any time during the study (alternatively the study may be terminated prematurely) in the events of unexpected, significant or unacceptable adverse event such that, in the opinion of Investigators would put them or other trial participant safety at risk.

### **10.12 Participant Stopping Criteria**

The stopping criteria refer to a participant stopping administration of the IMP. The withdrawal of a participant from the study may include the following reasons:

- Participants withdrawal of consent
- Non-compliance with the protocol
- Occurrence of an AE or change in medical status or an incidental finding that leads the Investigator concerned about the participant's welfare
- Pregnancy during the study
- Inability to continue, loss to follow-up
- The termination of the study by the Sponsor

If a participant is withdrawn from the study, they will be asked to undergo the early termination visit (visit 7, day 279) study procedures if applicable.

If enrolled participants prematurely discontinue the study or do not comply with the protocol, additional participants may be enrolled as replacement participants and assigned to the same treatment sequence at the discretion of the Principal Investigator. A maximum of two GBA positive and two GBA negative participants may be enrolled as replacement participants.

### **10.13 Intra-participant Dose Escalation Stopping Criteria**

Dose escalation will be halted and reviewed by the TMG if:

- a serious adverse event (SAE) occurs in 1 or more participants receiving ambroxol that is considered at least possibly related to study drug;
- two or more severe adverse events occur in a group for subjects receiving ambroxol that are considered at least possibly related to study drug;
- A formal decision will be sent to the sponsor to restart dose escalation (if deemed appropriate). A participant already on the dose escalation regime will continue if no adverse reactions have occurred.

### **10.14 Participant Termination Criteria**

The termination criteria refer to a participant stopping the study drug and all assessments and visits. The Investigator can terminate participants from the study for any of the following reasons:

- Participants withdrawal of consent
- Inability to continue, loss to follow-up
- Death

Participants who terminate the study for any reason will not be allowed to return to the study drug or study assessments at any time.

### 10.15 Participant Withdrawal and Termination

Participants have the right to withdraw from the study at any time for any reason, without prejudice to their standard of care medical care. Additionally, the Investigator may discontinue a participant from the IMP or terminate the participant from the study.

### 10.16 Assessment of Compliance and Adherence

The participants will be instructed to return all (used and un-used) IMP packages at each clinic visit for compliance check. The returned IMP will be collected from the CI/PI or the PI-delegated member of the research team from the participant at Visit 5 (day 93) and Visit 6 (day 186). The returned IMP will be counted to assess compliance in addition to telephone visits 2-10 where IMP compliance will be assessed.

### 10.17 Post-trial IMP Arrangement

There will be no arrangements for participants to receive additional IMP on study completion.

### 10.18 Definition of End of Trial

The end of trial is the date of the last participant's last visit or last participant's last telephone follow up visit.

## 11. Recording and Reporting of Adverse Events and Reactions

Collection, recording and reporting of adverse events (including serious and non-serious events and reactions) to the sponsor will be completed according to the sponsor's SOP (JRO/INV/S05).

### 11.1 Definitions

| Term                                                    | Definition                                                                                                                                                                                                                                                                   |
|---------------------------------------------------------|------------------------------------------------------------------------------------------------------------------------------------------------------------------------------------------------------------------------------------------------------------------------------|
| Adverse Event (AE)                               | Any untoward medical occurrence in a patient or clinical trial subject administered a medicinal product and which does not necessarily have a causal relationship with this treatment.                                                                                       |
| Adverse Reaction (AR)                            | Any untoward and unintended response in a participant to an investigational medicinal product which is related to any dose administered to that participant.

This includes medication errors, uses outside of protocol (including misuse and abuse of product) |
| Serious Adverse Event (SAE),
Serious Adverse | Any adverse event, adverse reaction or unexpected adverse reaction, respectively, that:                                                                                                                                                                                      |

|                                                                                                                                                                                                                                                                                                                                                                                                                                           |                                                                                                                                                                                                                                                                                                                                                                                                                              |
|-------------------------------------------------------------------------------------------------------------------------------------------------------------------------------------------------------------------------------------------------------------------------------------------------------------------------------------------------------------------------------------------------------------------------------------------|------------------------------------------------------------------------------------------------------------------------------------------------------------------------------------------------------------------------------------------------------------------------------------------------------------------------------------------------------------------------------------------------------------------------------|
| Reaction (SAR) or Unexpected Serious Adverse Reaction                                                                                                                                                                                                                                                                                                                                                                              | 
results in death,
 
is life-threatening*,
 
requires hospitalisation or prolongation of existing hospitalisation**,
 
results in persistent or significant disability or incapacity, or
 
consists of a congenital anomaly or birth defect
                                                                                                                                                        |
| 
*A life- threatening event, this refers to an event in which the participant was at risk of death at the time of the event; it does not refer to an event which hypothetically might have caused death if it were more severe.
 
** Hospitalisation is defined as an in-patient admission, regardless of length of stay. Hospitalisation for pre-existing conditions, including elective procedures do not constitute an SAE.
 |                                                                                                                                                                                                                                                                                                                                                                                                                              |
| Important Medical Event                                                                                                                                                                                                                                                                                                                                                                                                            | 
These events may jeopardise the subject or may require an intervention to prevent one of the above characteristics/consequences. Such events should also be considered 'serious'.
                                                                                                                                                                                                                                     |
| Unexpected adverse reaction                                                                                                                                                                                                                                                                                                                                                                                                        | 
An adverse reaction the nature and severity of which is not consistent with the information about the medicinal product in question set out:
 
(a) in the case of a product with a marketing authorization, in the summary of product characteristics for that product,
 
(b) in the case of any other investigational medicinal product, in the investigator's brochure relating to the trial in question.
 |
| Suspected Unexpected Serious Adverse Reaction (SUSAR)                                                                                                                                                                                                                                                                                                                                                                              | 
An unexpected adverse reaction which is also categorised as serious.
                                                                                                                                                                                                                                                                                                                                                  |

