## 7. Eligibility Criteria

### 7.1 Study Population

All participants who are recruited to this study shall have a confirmed diagnosis of PD. There will be no exceptions to eligibility requirements and all participants must fulfil the inclusion criteria.

Twenty PD participants (10 *GBA* positive & 10 *GBA* negative) will be enrolled into the study. If enrolled and participants prematurely discontinue the study, up to 4 additional participants (2 *GBA* positive and 2 *GBA* negative) may be enrolled as replacement participants.

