### 7.3 Participant Inclusion Criteria

1. Male or female;
2. Age  $\geq 40$  and  $\leq 80$  years of age;
3. Confirmed diagnosis of Parkinson disease at any time; and Hoehn and Yahr criteria, confirmed staged between I – III, inclusive;
4. Able and willing to provide informed consent prior to any study related assessments and procedures at screening visit 1;
5. Capable of complying with all study procedures, including fasting lumbar puncture;
6. Willing to provide a blood sample for screening genomic for Parkinson Disease related DNA analysis and/or consent to Investigators obtaining and using participants previous DNA results if applicable;
7. Willing and able to self-administer oral ambroxol medication, from day 1 to 186 (at 60 mg TID (day 1-7), 120 mg TID (day 8-14), 180 mg TID (day 15-21), 300 mg TID (day 22-28) and 420 mg TID (day 29-186));
8. Able to travel to the participating study site;
9. A female participant is eligible to participate if she is of:
  - Non-childbearing potential defined as pre-menopausal females with a documented tubal ligation or hysterectomy; or postmenopausal defined as 12 consecutive months of spontaneous amenorrhea, at least 6 weeks post-surgical bilateral oophorectomy (with or without hysterectomy) or post tubal ligation. In questionable cases, menopausal status will be confirmed by demonstrating levels of follicle stimulating hormone (FSH) 25.8 – 134.8 IU/L and oestradiol  $< 201$  pmol/l at entry.
  - Women of child-bearing potential must use accepted contraceptive methods (listed below), and must have a negative serum at screening visit 1 and urine pregnancy tests at subsequent visits if applicable. An additional pregnancy test will be performed, and results obtained, prior to administration of the first dose of ambroxol.

Accepted contraception methods:

- True abstinence: When this is in line with the preferred and usual lifestyle of the participant. [Periodic abstinence (e.g., calendar, ovulation, symptothermal, post-ovulation methods) and withdrawal are not acceptable methods of contraception].

Contraceptive Methods with a Failure Rate of  $< 1\%$ :

- Oral contraceptive, either combined or progestogen alone;
- Injectable progestogen;
- Implants of levonorgestrel;
- Estrogenic vaginal ring;
- Percutaneous contraceptive patches; -

- Intrauterine device (IUD) or intrauterine system (IUS) that meets the <1% failure rate as stated in the product label;

Please note:

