## 11.8 Seriousness

All events will be assessed for seriousness as defined for a SAE in section 11.1

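### The hospitalisation footnote in section 11.1 keeps an unplanned admission for worsening Parkinson disease from being serious on that ground, so a single related admission can miss SAE reporting and the one-SAE halt limb

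*Protocol*

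**What the plan says.** Section 11.1 makes an event serious if, among other criteria, it requires or prolongs hospitalisation. A footnote to that criterion first sets a wide scope: "Hospitalisation is defined as an in-patient admission, regardless of length of stay". It then takes some admissions out: "Hospitalisation for pre-existing conditions, including elective procedures do not constitute an SAE".

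Three other places determine what the footnote does.

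- **Who it covers.** Section 7.1: "All participants who are recruited to this study shall have a confirmed diagnosis of PD". Inclusion criterion 3 in section 7.3 repeats the requirement: "Confirmed diagnosis of Parkinson disease at any time".
- **How far it binds.** Section 11.8: "All events will be assessed for seriousness as defined for a SAE in section 11.1".
- **What depends on it.** Under section 10.13, escalation is halted and reviewed if "a serious adverse event (SAE) occurs in 1 or more participants receiving ambroxol that is considered at least possibly related to study drug". A second limb of the same section is met by two or more severe adverse events that are at least possibly related.

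Section 11.1 also has a row for important medical events, which are to be treated as serious: "These events may jeopardise the subject or may require an intervention to prevent one of the above characteristics/consequences".

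**The concern.** An exclusion of this kind normally keeps admissions arranged before the trial, or elective procedures for a stable condition, out of the SAE reports. This one is wider. Elective procedures appear only as an example, and neither a planned admission nor an unchanged condition is required. Because the disease under study is itself a pre-existing condition in all participants, the footnote reaches the admissions that are most specific to this population.

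Safety and tolerability are a secondary objective, and the trial is open label with no control arm. The Trial Management Group that oversees it consists of the investigator and the research team (section 12.4), so the SAE form is the main fast route to the sponsor. An event left out of the SAE class does not start the 24-hour report in 11.9, cannot be assessed as a SUSAR under 11.1 and 11.10, and does not count under the first limb of 10.13. Section 10.7 also uses SAE status as a condition when it describes dose reduction. Any misclassification runs in one direction, towards a safer-looking drug.

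**Working it through.** The plan states no figure on this point, so the check is mainly of the text. The numbers at the end are illustrations.

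**Following one event through the protocol.** Take an unplanned in-patient admission for worsening Parkinson disease during dosing, judged possibly related to ambroxol.

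1. *Is it an adverse event?* Yes. The definition in 11.1 is broad and has no exception for the underlying disease. It is recorded under 11.2.
2. *Is it serious through hospitalisation?* It is an in-patient admission, but for a condition present at entry, so the footnote says no. Section 11.8 sends the assessor back to this same definition, and no later section restores the event.
3. *Is it serious by another criterion?* Yes if it is fatal, life-threatening or causes persistent or significant disability. It may also be an important medical event. That needs a judgement, made against an explicit sentence saying that such an admission is not an SAE, so two investigators could classify the same case differently.
4. *If step 3 gives no*, the event has no 24-hour report, no SUSAR assessment and no place in the SAE count.
5. *Does it reach section 10.13?* Not the first limb, which needs an SAE. It can count toward the second limb if graded severe under 11.4. That limb does not ask for seriousness, but it needs two such events.

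For this case the footnote therefore changes the trigger from one event to two.

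**Size of that change (assumed rates).** Let n = 20 (section 13.3), and let p be the probability per participant of an admission that is severe, at least possibly related and serious on no other ground. The protocol gives no p, so a range is used.

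- One event is enough: P(X ≥ 1) = 1 − (1 − p)^20
- Two are needed: P(X ≥ 2) = 1 − (1 − p)^20 − 20p(1 − p)^19

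| Assumed p | One event is enough | Two are needed, n = 20 | Two needed within one genotype group, n = 10 |
|---|---|---|---|
| 1% | 18.2% | 1.7% | 0.4% |
| 5% | 64.2% | 26.4% | 8.6% |
| 10% | 87.8% | 60.8% | 26.4% |

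The last column applies if the group mentioned in the second limb is a genotype group. The protocol does not say.

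**How many admissions might be affected (assumed rates).** Assume 0.05 to 0.20 unplanned admissions per person-year for Parkinson disease or an entry comorbidity.

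- On treatment: 20 × 186 / 365.25 = 10.2 person-years. Expected admissions are 0.5 to 2.0, and 1 − exp(−mean) gives a 40% to 87% chance of at least one.
- To the day 279 visit: 20 × 279 / 365.25 = 15.3 person-years. Expected admissions are 0.8 to 3.1, with a 53% to 95% chance of at least one.

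Only the on-treatment figure bears on 10.13, which concerns participants receiving ambroxol. Neither figure is filtered for relatedness or for other seriousness criteria.

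**Effect on a reported SAE proportion.** The one-sided 95% Clopper-Pearson upper limit is 13.9% for 0/20 (1 − 0.05^(1/20)), 21.6% for 1/20 and 28.3% for 2/20. Leaving out one participant's event would lower the limit from 21.6% to 13.9%.

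**The case against.** A reader might infer that an admission for worsening Parkinson disease can never be an SAE and can never reach the halt rule. The documents do not support that. The footnote belongs to the hospitalisation criterion alone, so the fatal, life-threatening, disability and important-medical-event routes remain. Section 10.13 has a second limb that does not depend on seriousness. Its first limb already requires at least possible relatedness, so many such admissions would not trigger it under any SAE wording.

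Other points can be made for the protocol.

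- *A narrower reading.* Worsening on drug could be called a new event, with the footnote covering only the condition as it stood at entry. Section 8.6.6 treats clinically significant worsening of the ECG from baseline as an adverse event. But the footnote does not say this, and it concerns admission, which is a separate question from whether an adverse event occurred.
- *Other safeguards.* All adverse events are recorded from consent, and the outcome listed in 13.2 is adverse events, not SAEs. Section 10.11 allows treatment or the study to be stopped for a significant event without an SAE label. This stands: the event is not lost from the data. What can be lost is its fast reporting and its classification.
- *The sponsor's SOP.* Section 11 refers to one for adverse event reporting, and it may clarify the point. It is not available here, and the protocol's explicit sentence would still contradict it.
- *The rates.* They are assumed. Eligibility limited to Hoehn and Yahr stages I to III, and the exclusion of unstable conditions, may make such admissions uncommon. The protocol plans Bayesian credible intervals, not Clopper-Pearson limits. This stands, and the figures show scale only.

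**Conclusion.** The point holds in a limited form. As written, the footnote removes hospitalisation as a route to SAE status for worsening of any condition present at entry, and Parkinson disease is such a condition in all participants. One related, unplanned admission that meets no other criterion therefore goes without the 24-hour report, SUSAR assessment, a place in the SAE count and effect under the one-SAE limb of 10.13. It stays a recorded adverse event and may count toward the two-severe-event limb.

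This conclusion rests on the text and needs no assumed rate. The size does: at p = 5%, the chance of reaching the trigger is 64.2% with one event and 26.4% with two. That assumes every such event is graded severe, judged at least possibly related and serious on no other ground. The defect is in a protocol definition, so a later analysis plan would not cure it, and it should be corrected.

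**What to change.** Amend the footnote in section 11.1 so that:

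- the exclusion covers only admissions planned before consent, and elective procedures for a pre-existing condition that has not worsened since consent;
- an unplanned admission, or an admission for worsening of a pre-existing condition including Parkinson disease, meets the hospitalisation criterion.

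Then reconcile the footnote with the important-medical-event row in 11.1 and with section 10.13, so that the same admission cannot be classified in two ways. The content of the halt rule itself is not at issue here. Add one line to the SAE form guidance. Review any admissions already left out under the present wording and re-classify them.

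The cost is a short protocol amendment and a few more SAE reports, most of them likely to be rated unrelated.

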### 11.4 Severity

| Category | Definition |
|----------|------------|
|----------|------------|

|                 |                                                                                                                                                                     |
|-----------------|---------------------------------------------------------------------------------------------------------------------------------------------------------------------|
| Mild     | The adverse event does not interfere with the participant's daily routine, and does not require intervention; it causes slight discomfort                           |
| Moderate | The adverse event interferes with some aspects of the participant's routine, or requires intervention, but is not damaging to health; it causes moderate discomfort |
| Severe   | The adverse event results in alteration, discomfort or disability which is clearly damaging to health                                                               |

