## 11.9 Procedures for Recording and Reporting Serious Adverse Events

All serious adverse events (SAEs/SARs/SUSARs) will be recorded in the medical records and the CRF, and the sponsor's AE log. The CRF AE log of SAEs will be reported to the sponsor at least once a year.

All SAEs will be recorded from consent FPFV to LPLV. The LP will be optional to participants if they agree to undergo an LP at visit 7, day 279 the CSF sample will be sent for analysis and they will receive a safety telephone call within 5 days of visit 7 to record AEs.

All SAEs must be recorded on a serious adverse event (SAE) form. The CI/PI or designated individual will complete the sponsor's SAE form and the form will be preferably emailed to the Sponsor [[contact]](mailto:[contact]) and/or faxed on [name], within 24 hours of them becoming aware of the event. The CI/PI will respond to any SAE queries raised by the sponsor as soon as possible.

Completed SAE forms must be sent within 24 hours of becoming aware of the event to the Sponsor

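### The hospitalisation note in section 11.1 has no exception for worsening, so an unplanned, possibly related admission for worsened PD can, read literally, fall outside the SAE definition

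*Protocol*

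**What the plan says.** The SAE row of the definitions table in section 11.1 lists five consequences that make an event serious, hospitalisation among them. A note tied to that one criterion counts any in-patient stay, however short, and then adds: "Hospitalisation for pre-existing conditions, including elective procedures do not constitute an SAE". A separate row of the same table covers important medical events: "These events may jeopardise the subject or may require an intervention to prevent one of the above characteristics/consequences". These too are to be treated as serious.

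Section 11.8 makes this table the reference for all events: "All events will be assessed for seriousness as defined for a SAE in section 11.1". Section 7.1 fixes the population: "All participants who are recruited to this study shall have a confirmed diagnosis of PD".

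Three later rules depend on the serious label:

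- Section 10.13 halts escalation for Trial Management Group (TMG) review if "a serious adverse event (SAE) occurs in 1 or more participants receiving ambroxol that is considered at least possibly related to study drug". A second trigger applies if "two or more severe adverse events occur in a group for subjects receiving ambroxol", again at least possibly related.
- Section 11.9 sets the sponsor's clock: "Completed SAE forms must be sent within 24 hours of becoming aware of the event to the Sponsor".
- Section 11.1 defines a SUSAR as an unexpected reaction that is also serious. Section 11.10 gives the sponsor 7 days to notify the regulator and ethics committee if it is fatal or life-threatening, and 15 days otherwise.

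**The concern.** An exemption of this kind normally keeps planned surgery and routine admissions for stable disease out of the SAE count. This one is wider. It names the whole class of pre-existing conditions, and that class includes the study disease in every participant. Worsened parkinsonism is a plausible reason for an unplanned admission in this population, and a possible drug effect that the trial should be able to see. The top dose is 1260 mg a day, against over-the-counter doses of up to 120 mg a day (section 2.1).

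What is at stake is whether such an admission reaches the TMG and the sponsor by a fixed rule or only by the assessor's judgement. The TMG consists of the investigator and the research team (section 12.4), so the SAE form and the SUSAR notice are the main routes with a fixed time limit by which an event leaves the team.

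**Working it through.** This is a check of wording; the only arithmetic is a count of events against the thresholds in 10.13.

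1. **Scope of the exemption.** The note introduces elective procedures as one member of the exempt class, not as its limit. It has no condition on whether the admission was planned, whether the illness was stable, or whether ambroxol is suspected. Elsewhere, the protocol treats worsening from baseline as an event only for ECG findings (8.6.6), and then as an AE. No section restores seriousness for a pre-existing condition that deteriorates.

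2. **Who is covered.** PD is pre-existing in all 20 planned participants, and in up to 20 + 4 = 24 if all replacements in section 7.1 are used.

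3. **Which definition governs.** Section 11.8 points to 11.1, so the note applies to every seriousness assessment.

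4. **One event traced both ways.** Take one unplanned admission for worsened PD, judged possibly related, meeting no other seriousness criterion and not classed as an important medical event.

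| Rule | Note read literally | Worsening counted as an SAE |
|---|---|---|
| 10.13, SAE trigger (needs 1) | 0 of 1: not met | 1 of 1: met |
| 10.13, severe-event trigger (needs 2) | 1 of 2 if graded severe; 0 of 2 if moderate | not needed |
| 11.9, form to sponsor | no time limit fixed in this protocol | 24 hours |
| 11.10, SUSAR notice | cannot apply, because not serious | 15 days, if unexpected |

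   A moderate grade is possible for an admission, because section 11.4 includes in that grade an event that interferes with the routine "or requires intervention, but is not damaging to health". Only the 15-day clock is at stake: a fatal or life-threatening event is serious by those criteria whatever the note says.

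5. **Expectedness.** Section 11.6 judges it against section 4.8 of the SmPC, which is not available here. The protocol's own risk table (section 3) lists ten risks of the drug, and worsening of PD is not one of them. If the SmPC list matches that table, which is an assumption, a related serious worsening would be unexpected and so a SUSAR. If the SmPC lists it, the SUSAR consequence disappears and the other two remain.

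6. **Other routes to serious.** The note qualifies the hospitalisation criterion only. Death, threat to life, lasting disability and the important-medical-event row remain open. What is left uncovered is an unplanned, possibly related admission that the assessor does not place under any of these.

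**The case against.** The literal reading is not the only one. Worsening on treatment is itself an untoward occurrence and so an AE. An admission for it can be read as an admission for that new event and not for the condition brought into the trial; the ECG clause in 8.6.6 shows the authors thinking that way. An experienced investigator may well apply the note only to elective stays. This stands as a reason to call the text ambiguous, but it does not supply the missing words.

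The important-medical-event row is the strongest point. It belongs to the same definition that 11.8 invokes, and many unplanned, possibly drug-related admissions would meet it. It is nevertheless a judgement that the assessor has to make against a flat statement that the admission is not an SAE.

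Other safeguards need no SAE label. Section 10.11 allows a participant to be discontinued, or the study ended early, for an unexpected, significant or unacceptable event. Section 10.12 allows individual stopping for any AE that worries the investigator. Section 11.13 requires written notice to the regulator, the ethics committee and the sponsor within 3 days of an urgent safety measure. Section 11 also defers to a sponsor procedure that is not shown and may deal with worsening. The first two are discretionary, the third starts only once a measure has been taken, and the content of the last is unknown.

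A reader might infer that related admissions for worsened PD would go unrecorded, that the protocol forbids calling them serious, or that no number of moderate ones could ever stop escalation. The documents support none of these. All AEs are recorded (11.2), the routes above can make such an event serious, and the last statement is true only of the two automatic triggers in 10.13.

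**Conclusion.** The point holds in a limited form. The exemption in 11.1 is unqualified, the study disease falls inside it, and three rules turn on the label it removes. For an affected admission, the automatic halt threshold moves from one related event to two if severe, with moderate events not counting. The sponsor's 24-hour clock is replaced by no limit fixed in this protocol, and a 15-day notice may not start.

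This rests on the literal reading of the note, on the assessor not using another criterion or the important-medical-event row and, for the SUSAR consequence alone, on worsening of PD being unexpected against the SmPC. The halt matters only while some participants are still escalating or have yet to start; the reporting consequence applies throughout. The protocol gives no admission rate, so neither a frequency nor a probability can be attached. It is a gap in a safety definition, narrowed but not closed by the other provisions, and worth correcting because the correction is so small.

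**What to change.** In section 11.1, restrict the exemption to planned or elective admissions for conditions that have not worsened since consent, and add a sentence such as: *An unplanned admission for worsening of a pre-existing condition, including PD, is an SAE.* Sections 10.13, 11.8, 11.9 and 11.10 then work as written and need no change.

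The cost is one or two sentences in a protocol amendment, and a few more SAE forms and TMG reviews. If investigators already read the note as covering elective stays only, practice does not change.
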